#### **4.9 Data to be included on the case report forms (CRF)**

##### ***Study participants***

After initial stabilization, participants recruited to the trial will have a screening form completed, according to inclusion and exclusion criteria. Patient age, co-morbidities, nutrition status (weight and height), malaria rapid diagnostic test result, anemia, methemoglobin level, and willingness to participate in the trial will be documented on the screening form and will be the basis of deciding on whether a child is eligible for the study. Eligible, consenting participants will then undergo a full history and physical

examination, the results of which will be recorded on the CRF. Study entry blood work will include the following, and a checklist on the CRF will be completed to ensure that the appropriate specimens have been collected for laboratory testing:

- CBC and differential
- Electrolytes
- Creatinine
- Lactate
- Venous blood gases
- Blood culture
- CSF gram stain and culture (as appropriate)
- CSF cell count and differential (as appropriate)
- HIV point-of-care test
- Serum and plasma sample for Ang-2

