***Time to sit unsupported***

Trial nurses will document at the end of each shift whether the patient is able to sit unsupported and the time to achieve this endpoint will be derived from these data.

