## **5 SELECTION AND WITHDRAWAL OF SUBJECTS**

### **5.1 Inclusion criteria**

1. Age 1-10 years

2. Positive malaria rapid diagnostic test in the presence of selected features of severe malaria.
3. Willing and ability to complete follow up schedules for the study – 14 day and 6 months after hospital discharge.

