## **5.2 Exclusion criteria**

1. Baseline methemoglobinemia (>2%)
2. Known renal, cardiac, or hepatic disease or other chronic illnesses like diabetes, epilepsy, cerebral palsy, clinical AIDS, suspected or known hemoglobinopathy (e.g., sickle cell anemia, G6PD deficiency).
3. Suspected bacterial meningitis.
4. Patient already received parenteral quinine in the ED prior to eligibility assessment.
5. Patient unlikely to tolerate delivery mask for more than 24 hours.
6. Severe malnutrition
7. Severe malarial anemia (Hb <50g/L) without other signs of severe malaria.

---

 repeated seizures (two or more generalized seizures in 24 h); prostration (in children 1 year and older, the child is unable to sit unsupported or stand although was able to before the illness; impaired consciousness (Blantyre Coma Score <5 in children 1 to 4 years, GCS <14 for children ≥ 5 years); respiratory distress: sustained nasal flaring, deep breathing or intercostal/subcostal retractions.

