**Secondary outcomes**

*Mortality.* Analysis will follow standard methods in other clinical trials for malaria[64, 81, 82]. Mortality at 48 h and 14 days will be coded as a binary variable. Absolute and relative risk reduction will be reported with binomial 95% confidence intervals. Analysis will be by chi-squared test or Fisher exact test if the expected number of deaths is less than five in one or both treatment groups. In addition, we will present Kaplan-Meier survival curves comparing patients treated with iNO compared to placebo.

Time to death will be analysed using survival analysis (Cox proportional hazard model for difference between treatment arms).

*Time to recovery.* Among survivors (subgroup analysis of randomized participants), recovery times will be analysed by survival analysis (Cox proportional hazard model for difference between treatment arms). Time to sit unsupported, time to coma resolution (in the subset of patients with coma at study admission) and time to discharge will be documented by treating clinicians (blinded to intervention). Time to fever resolution, defined as the time required to achieve a temperature  $<38^{\circ}\text{C}$  and the time to maintenance of temperature  $<38^{\circ}\text{C}$ , will be determined from frequent vital sign monitoring. The time required to achieve a reduction in parasite density of 50%, 90% and to undetectable levels will be determined from daily blood smears. Results will be expressed as the median time to each event, with 95% confidence intervals.

*Additional biomarkers* (continuous variables, multiple measurements longitudinally collected) will be analysed using mixed-effects linear models, with the raw value or log-transformed value of the biomarker level as the dependent variable, as appropriate.

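### Time to sit unsupported is analysed in all survivors, including children who can already sit at entry; only coma resolution is limited to children with the deficit

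*Protocol*

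**What the plan says.** Protocol section 9.1 (Secondary outcomes, Time to recovery) sets the analysis population: "Among survivors (subgroup analysis of randomized participants), recovery times will be analysed by survival analysis", by Cox model, with the median time to each event reported. The only at-risk condition sits inside the list "Time to sit unsupported, time to coma resolution (in the subset of patients with coma at study admission) and time to discharge", where it applies to coma alone. Time to sit, fever resolution and the parasite times in the same paragraph have none. Coma resolution is not in the endpoint lists of sections 4.1 and 7.1, whereas the endpoints without the condition are.

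Entry (section 5.1) asks for "Positive malaria rapid diagnostic test in the presence of selected features of severe malaria". The footnote printed under section 5.2 begins "repeated seizures (two or more generalized seizures in 24 h); prostration (in children 1 year and older, the child is unable to sit unsupported" and goes on to impaired consciousness and "respiratory distress: sustained nasal flaring, deep breathing or intercostal/subcostal retractions".

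The screening items in section 4.9 are "Patient age, co-morbidities, nutrition status (weight and height), malaria rapid diagnostic test result, anemia, methemoglobin level" and willingness to take part, so neither temperature nor parasite count is named. Sitting is checked by the nurses once per shift (section 4.9), and the record is "whether the patient is able to sit unsupported and the time to achieve this endpoint will be derived from these data". Section 4.9 defines fever resolution as a temperature below 38°C for at least 24 hours. Section 9.1 names two fever measures: reaching below 38°C, and maintaining it.

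**The concern.** A time-to-recovery comparison is informative only in children who have something to recover from. A child enrolled for repeated seizures or respiratory distress may be able to sit when study gas starts. Such a child adds an event at the first possible moment, in equal expectation in both arms, whatever the gas does. The hazard ratio then depends partly on case mix, and a real acceleration of recovery could be missed. These endpoints carry the clinical efficacy aim (section 3, aim 2).

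The authors dealt with this for coma and not for sitting, so the plan is uneven rather than merely silent. Timing also matters: section 9.6 says departures from the analyses described in the protocol will be reported as post hoc and exploratory, so a restriction added later risks that label.

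**Working it through.** **Plan's own figure.** None exists for a recovery endpoint. The only sample size (section 9.2) is for Ang-2, so there is nothing to reproduce here.

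**Inputs from the protocol.** 180 children, about 90 per arm (section 9.2). Mortality about 20% (section 8.1), so survivors = 180 × 0.80 = 144, or 72 per arm. Shifts of 8 hours (section 4.9, Intervention). Two-sided 5% level.

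**Assumptions not in the protocol.** True hazard ratio 1.5 or 1.7 among children unable to sit; exponential times with a control median of 36 h; a share f of both arms already able to sit, from 0 to 50%.

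**Step 1: power if only children at risk are analysed.** Schoenfeld's formula with equal arms is power = Φ(√D/2 × ln HR − 1.96), with D = 144 × (1 − f) events.
- f = 0, HR 1.5: √144/2 × 0.405 − 1.96 = 0.47, power 68%. HR 1.7: 6 × 0.531 − 1.96 = 1.22, power 89%.
- f = 50%, D = 72, HR 1.5: 4.24 × 0.405 − 1.96 = −0.24, power 41%. HR 1.7: 4.24 × 0.531 − 1.96 = 0.29, power 61%.

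**Step 2: all survivors against children at risk.** 300 simulated trials per row, times rounded up to 8-hour readings, Efron ties, children able to sit entered as events at time 0.

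| True HR | Share f | All survivors: HR, power | At risk only: HR, power |
|---|---|---|---|
| 1.5 | 0% | 1.50, 66% | 1.50, 66% |
| 1.5 | 10% | 1.42, 54% | 1.49, 60% |
| 1.5 | 30% | 1.33, 35% | 1.53, 51% |
| 1.5 | 50% | 1.20, 20% | 1.51, 37% |
| 1.7 | 0% | 1.72, 87% | 1.72, 87% |
| 1.7 | 10% | 1.64, 83% | 1.75, 85% |
| 1.7 | 30% | 1.45, 58% | 1.73, 76% |
| 1.7 | 50% | 1.30, 29% | 1.72, 60% |

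The standard error of each power is at most √(0.5 × 0.5/300) = 2.9 points. The 10% rows therefore show direction, not a precise gap. The at-risk column agrees with step 1.

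**Step 3: scoring at the first shift instead of time 0.** In a separate set of 1000 runs (true HR 1.6, control median 32 h, f = 35%), time-0 scoring gives HR 1.35 and power 42%. First-shift scoring gives HR 1.37 and power 46%. Children at risk give 1.61 and 59%. The loss is nearly the same under either scoring.

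**Step 4: control median.** With share f at time 0, the proportion not yet recovered at t is (1 − f) × 2^(−t/36). Setting this to 0.5 gives t = 36 × log2[2(1 − f)]: 30.5 h at f = 10%, 17.5 h at 30% and 0 h at 50%, before rounding to shifts.

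**Step 5: the other endpoints, by reading.** No simulation was run for these.
- *Parasites.* A 50% or 90% fall is undefined at a zero count. Time to undetectable is already met.
- *Fever, first reading below 38°C.* A child below 38°C at entry has already met it.
- *Fever, sustained for 24 hours.* A child below 38°C at entry can still rise above it, so the endpoint is not met at time 0.

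**The case against.** **The protocol never says that a child already able to sit is an event at time 0.** That is correct, and risk-set details are often left to an analysis plan. If the software drops zero times, the dilution disappears. But the set analysed is then no longer the stated one, and first-shift scoring, which fits how sitting is recorded, gives almost the same loss. The uneven rule is in the protocol itself.

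**A reader might infer that every afebrile child resolves at time 0.** The protocol does not support this for the sustained definition in section 4.9. Screening follows initial stabilisation and antipyretics are allowed (section 6.2), so a single reading below 38°C at entry is compatible with later fever. Those children carry information and should stay in.

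**A reader might infer that zero-count children dilute all the parasite endpoints.** They do not. The 50% and 90% falls have no value in such a child, so the gap there is a missing definition. Only time to undetectable could be diluted, and the share of rapid-test-positive children with a zero count is not given.

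**That one sign suffices for entry is a reading.** No minimum number is stated. The list reads as alternatives, and section 9.7 treats cerebral malaria and respiratory distress as alternative syndromes. However, two of the listed features, prostration and impaired consciousness, make being able to sit less likely, so a high share cannot be presumed.

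**The effect is conservative and the endpoints are secondary.** Both are true. The flaw does not create a false benefit and does not touch the Ang-2 analysis or the sample size.

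**Conclusion.** The point holds for time to sit unsupported. Analysing all survivors biases its hazard ratio toward 1 and shortens its median, and costs more power than the events lost by restriction in every scenario with such children. The loss is small if about 10% can already sit and large near 50%. The protocol does not say where in that range the trial would fall, and the hazard ratio and control median are also assumed, so no single figure should be quoted as the expected loss.

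For parasite times the need is a defined at-risk set. For fever it applies only to the first-reading measure. This is worth correcting before analysis, but it is not a threat to the trial's primary conclusion.

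**What to change.** In section 9.1, extend the coma rule as follows and report the number at risk per arm for each endpoint.

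- **Time to sit:** children recorded as unable to sit at the eligibility assessment, before randomisation. The end-of-shift record should not be used for this, since the first one may follow randomisation.
- **Parasite times (50%, 90%, undetectable):** children with a positive count on a film taken before study gas starts. The entry blood work in section 4.9 lists no film, so confirm that it is collected.
- **Fever:** for time to the first temperature below 38°C, children at or above 38°C at entry. For the sustained 24-hour definition, keep all survivors.

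The cost for sitting is wording, because prostration is already assessed for eligibility; the form should show ability to sit for every child, including those who enter on another sign. For parasites and fever, the baseline film and temperature must be confirmed as taken in time. The downside is fewer children per endpoint. Selecting on status before randomisation keeps the comparison between arms fair.

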***Secondary endpoints:***

***48 hour and 14-day mortality***

The CRF will document whether the patient was alive or deceased or lost to follow-up at 48 hours after admission, and at the 14-day follow-up visit.

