***Serious Adverse Event or Serious Adverse Drug Reaction***

*A serious adverse event (experience) or reaction is any untoward medical occurrence that at any dose:*

- *results in death,*
- *is life-threatening,*
- *requires prolongation of existing hospitalisation, or*
- *results in persistent or significant disability/incapacity*

In this trial of critically ill children hospitalized with severe malaria, mortality is expected to occur in approximately 20% of participants who receive standard medical care[90].

Monitoring serious adverse events during the trial is therefore complicated by the fact that death is part of the natural progression of disease, even under conditions of optimal clinical care (Uganda standard of care). We propose to monitor mortality continuously to detect variations above the baseline expected mortality rate, to allow for early implementation of corrective actions, if required.

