### **8.3 Procedures for eliciting reports of and for recording and reporting adverse event and intercurrent illnesses**

SAE forms will be made available to the DSMB, ethics boards and regulatory authority according to their requirements, which differ between each body. Accordingly, all SAEs will be reported to MUREC and the Uganda NDA as soon as possible, but within 15 days of the event. Unexpected SAEs will additionally be reported to the DSMB chairperson, MUREC, NDA, Jinja Hospital REB (as soon as possible, but within 15 days of the event). Fatal and life-threatening unexpected SAEs will be reported to the DSMB chairperson, MUREC, NDA, Jinja Hospital REB as soon as possible, but within at most 7 calendar days. Finally, SAEs that are unexpected, related or possibly related to the study intervention, and suggest an increase in risk to study participants or others will also be reported to the UHN REB (Toronto).

All SAEs that occur during hospitalization will be reported as described above.

Regarding SAEs that occur after hospital discharge, reports will be issued as described above for events occurring up to day 14 of the study (i.e., after hospital discharge, out to 14 days post-enrolment).

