*Neurocognitive outcomes.* Statistical analysis of neurocognitive outcomes will be performed as follows. Frequencies of overall cognitive and neurologic deficits in children treated with iNO and children receiving placebo will be compared by  $X^2$  test or Fisher's exact test. Differences in cognitive areas affected in the two age groups (18 mo-4 years, 5-10 years) will be assessed by comparing frequency of individuals with deficits in each area by  $X^2$  test or Fisher's exact test. This will also serve as the best surrogate of level of impairment in a particular area in one age group vs another, since the type of testing for each cognitive area will be different for the two age groups, so no direct comparison of level of impairment will be possible across age groups. For individual tests, age-adjusted z-scores (determined from normative data in previous studies among healthy community controls) will be analyzed by means of mixed-effects models to examine study group differences in relation to neurocognitive outcomes. The models will provide estimated mean differences between children treated with iNO to placebo controls.

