## **9.2 Number of subjects planned to be enrolled**

We will enrol 180 patients (approximately 90 in each treatment arm).

Based on a recent clinical trial of L-arginine as adjunctive treatment for severe malaria, among patients who subsequently recovered, Ang-2 decreased by 2700pg/mL/day (95%CI 1800-3600pg/mL/day)[33]. We assume that a 50% change in this parameter would represent a clinically significant therapeutic effect. By standard calculations for normally distributed data, 80 patients per group will provide 80% power to detect a difference between two treatment arms of 1350pg/mL/day at  $p=0.05$  (two-sided). This corresponds to a 50% difference in the rate of change of Ang-2 between the arms. To account for possible dropout, loss to follow-up, and/or non-evaluable data of 10% of patients, approximately 90 patients per study arm are required.

However, these calculations do not reflect the analytic plan. Therefore, a simulation study was performed. A number of assumptions needed to be made, such as within patient correlation and Ang-2 variability. Patient Ang-2 data were simulated using a

multivariate normal distribution. A simple autoregressive correlation structure was used with correlations of 0.75, 0.5 and 0.25 for lags 1, 2 and 3 respectively. In previous studies, variability appears proportional to the mean[33]. Simulations were run with three different relationships where the standard deviation was taken to be 40%, 50% and 80% of the Ang-2 mean at each time point. Both groups were assumed to start at Ang-2 levels of 15,000 pg/mL and the average values at each of days 1, 2 and 3 based on the hypothesized slopes of Ang-2. One thousand replications were performed at each standard deviation relationship and treatment effect. The mixed effects models were fit and the likelihood ratio test was used to test the hypothesis of no time by treatment interaction at the 5% level (two tailed). Table 4 shows the results of the power simulations.

Table 4: Power simulations for 90 patients per group

| Standard Deviation
(% of mean) | Slope Difference               |                                        |                                        |
|-------------------------------------------|---------------------------------------|----------------------------------------|----------------------------------------|

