### **9.3 Level of significance to be used**

The threshold for statistical significance will be  $\alpha=0.05$ .

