## **APPENDIX 1. STATISTICAL THRESHOLDS FOR MONITORING MORTALITY**

The frequency of deaths and severe adverse events in the trial will be carefully monitored for deviations from expected baseline level using statistical control charts.

The control chart is a commonly used tool to monitor output of processes in a variety of settings, including clinical trials[95]. This method continuously follows a process outcome (e.g., patient mortality), allowing early detection of deviations from a state of “statistical control,” thereby prompting a search for assignable causes.

For each consecutive group of 10 patients (irrespective of group assignment), the mortality will be computed and plotted on the control chart. Points lying above the upper control limit (UCL) will trigger trial halting and a review of trial procedures for possible causes of elevated mortality and initiating corrective measures. The probability of a type I error (“false alarm,” halting the trial unnecessarily) and type II error (when the chart fails to indicate the presence of a deviation from baseline mortality) under this scheme can be quantified with some assumptions.

We determined an expected level of mortality from a literature review of clinical trials involving severe malaria in children in sub-Saharan Africa[90]. The mortality in these controlled trials ranged from 6-29%, with a median of 19%. Data from Uganda indicates that the mortality associated with severe malaria is comparable (16% of children with impaired consciousness, and 21% of children with deep acidotic breathing)[80]. The mortality rate observed in the clinical trial is therefore expected to be approximately

20%, with random variation about this baseline value as we sample small groups of patients for monitoring purposes.

The upper control limit was determined using a traditional approach under assumptions that the distribution of mortality will follow a normal approximation to the binomial distribution, and balancing the “detection capacity” (minimizing type II error rate) while minimizing the probability of “false alarms” (type I error rate). This yielded an upper control limit of 57%, or a threshold of 6 deaths in a sample of 10 patients.

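### The 6-month neurocognitive comparison has no rule for children who die, so it compares tested survivors only, and no vital-status item is scheduled after day 14

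*Protocol*

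**What the plan says.** Section 4.1 gives the neurocognitive endpoint a causal purpose: to find out whether iNO improves long-term outcome. Section 9.1 then fixes the analysis. "Frequencies of overall cognitive and neurologic deficits in children treated with iNO and children receiving placebo will be compared by" a chi-squared or Fisher's exact test, and age-adjusted z-scores go into mixed-effects models. It names no denominator and does not mention death.

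Section 8.1 states that "mortality is expected to occur in approximately 20% of participants who receive standard medical care". Appendix 1 gives the range behind that figure: "The mortality in these controlled trials ranged from 6-29%, with a median of 19" per cent.

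Section 9.5 sets missing-data rules for Ang-2, mortality, recovery times and other continuous variables. It has none for a binary deficit, and for continuous variables it does not separate death from other missingness. Section 9.1 explicitly restricts the recovery-time analyses to survivors, but says nothing similar for neurocognition.

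On vital status, section 4.9 has the CRF record whether the child is "alive or deceased or lost to follow-up at 48 hours after admission, and at the 14-day follow-up visit". The 6-month CRF is described only as holding test findings. Under section 8.3, SAE reports after discharge cover "events occurring up to day 14 of the study". Three other places carry no day-14 limit:
- Section 4.9 sends deaths to the CRF and an SAE form.
- Section 5.3(b) puts the reason for any non-completion on the CRF.
- Section 8.2 requires an SAE form for every death in the study.

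**The concern.** Children with a 6-month test result are a subset selected by survival, and survival is something iNO is meant to affect. The arms are comparable at randomisation. They need not be comparable among those alive and tested at 6 months. If iNO keeps alive some children who would otherwise have died, and those children have deficits more often than other survivors, the iNO arm's deficit rate rises although no child was harmed. The reverse can also happen: excess deaths among the most impaired children lower the measured deficit rate.

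The same applies to the z-scores. They are taken at the 6-month assessment, so a child who died before it contributes nothing to the model.

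What is at stake is the reading of the trial's only 6-month endpoint. A difference between arms could reflect who survived and not how well survivors fared, and the plan has no analysis that would separate the two.

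**Working it through.** **The plan's own figure.** The Protocol gives no power or expected deficit rate for this endpoint. Its 20% mortality is also the working figure in Appendix 1. With 20% mortality, P(6 or more deaths in 10) = 0.00637, and 1/0.00637 = 157 inspections, as stated there.

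**How many children are affected.** At 20%, 180 × 0.20 = 36 deaths, leaving 90 × 0.80 = 72 survivors per arm before any loss to follow-up. Over the 6-29% range in Appendix 1, deaths run from 180 × 0.06 = 10.8 to 180 × 0.29 = 52.2, and survivors per arm from 84.6 down to 63.9. These counts apply the same mortality to both arms.

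**Inputs for the bias.** Only the placebo mortality comes from the Protocol. The rest are assumptions.
- m0 = 20%, placebo mortality (section 8.1).
- m = 10% or 15%, iNO mortality (assumed).
- q = 15% or 25%, deficit rate in children who survive in either arm (assumed).
- s = 40%, 50% or 60%, deficit rate in rescued children, meaning those who survive only because of iNO (assumed).
- iNO has no other effect on deficit, and no child dies because of it (assumed).

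**Formulas.**
- iNO survivor deficit rate = [(1 − m0)q + (m0 − m)s] / (1 − m), compared with q on placebo.
- Death or deficit in all randomised: placebo m0 + (1 − m0)q; iNO m + (1 − m0)q + (m0 − m)s.

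**Worked example**, q = 25%, m = 10%, s = 50%: survivors (0.80 × 0.25 + 0.10 × 0.50)/0.90 = 0.25/0.90 = 27.8%, against 25.0% on placebo (22.5/81 against 18.0/72). Death or deficit: 0.10 + 0.20 + 0.05 = 35.0%, against 0.20 + 0.20 = 40.0%.

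**All settings** (s = 40 / 50 / 60%):

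| q | m | iNO survivor deficit, % | Shift from q, points | Death or deficit, placebo, % | Death or deficit, iNO, % |
|---|---|---|---|---|---|
| 15% | 10% | 17.8 / 18.9 / 20.0 | +2.8 / +3.9 / +5.0 | 32.0 | 26.0 / 27.0 / 28.0 |
| 15% | 15% | 16.5 / 17.1 / 17.6 | +1.5 / +2.1 / +2.6 | 32.0 | 29.0 / 29.5 / 30.0 |
| 25% | 10% | 26.7 / 27.8 / 28.9 | +1.7 / +2.8 / +3.9 | 40.0 | 34.0 / 35.0 / 36.0 |
| 25% | 15% | 25.9 / 26.5 / 27.1 | +0.9 / +1.5 / +2.1 | 40.0 | 37.0 / 37.5 / 38.0 |

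The survivor comparison shifts against iNO by 0.9 to 5.0 points, while death or deficit falls by 2 to 6 points. If m = m0, or if s = q, the shift is exactly zero.

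**Other direction.** Take iNO mortality 30%, q = 25%, and half of the extra deaths among children who would have been impaired. The survivor rate is (0.20 − 0.05)/0.70 = 21.4%, below 25%, while death or deficit rises from 40% to 0.30 + 0.15 = 45%.

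**Size against noise.** In the worked example the standard error of the survivor difference is √(0.25 × 0.75/72 + 0.278 × 0.722/81) = 0.071. For 15% against 20% it is √(0.15 × 0.85/72 + 0.20 × 0.80/81) = 0.061. The bias stays below one standard error in every setting.

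**Would the mortality test give warning?** For 20% against 10% with 90 per arm, two-sided 5%, normal approximation: (0.10 − 1.96 × 0.0532)/0.0527 = −0.08, a power of about 47%. A real survival difference of that size would be missed about half the time.

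**The case against.** The strongest reply is that a denominator and a rule for deaths in one secondary endpoint are ordinary SAP content, and the SAP is not shown. That limits the weight of the point but does not remove it. The Protocol itself fixes this comparison, sets missing-data rules for other outcomes in 9.5, and in 9.6 classes departures from its planned analyses as post hoc and exploratory. Nor can a SAP supply vital status that was not collected.

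A second reply is that mortality is not hidden: 9.1 analyses it by arm at 48 hours and 14 days, with Kaplan-Meier curves and a Cox model. This is fair, and it is why a survivor comparison shown beside mortality is defensible. It does not correct the deficit comparison, and the mortality test has limited power.

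A third is that the size follows from assumed inputs. That stands. Every row of the table assumes lower mortality on iNO and more impairment in rescued children, so the opposite signs of the two comparisons were built in and are not evidence that reversal is likely.

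Two stronger readings are tempting. A reader might infer from 4.9 and 8.3 that deaths after day 14 are recorded nowhere, so that a dead child looks the same as one who missed the visit. The documents do not support this. Sections 4.9, 5.3(b) and 8.2 would capture any later death the team learns of, and 8.3 limits when reports are issued, not what the site records. A reader might also infer that death or deficit should replace the survivor comparison. In the worked example death supplies 20 of the 40 placebo points and is already analysed separately, so a pure mortality effect could then be read as a neurocognitive benefit.

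**Conclusion.** The point holds in limited form. As written, 9.1 compares tested survivors without saying so, for an endpoint whose stated purpose is causal, in a trial that expects about 20% mortality. The comparison is biased if iNO changes mortality and the children whose survival it changes have a different deficit rate from other survivors. Both conditions are needed. Under the assumed inputs the bias is about 1 to 5 percentage points, less than one standard error at this sample size. The direction depends on the direction of the mortality effect and on which children it touches.

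On data capture, the gap is narrow. No vital-status item is scheduled after day 14, so a child who does not return and whose family is not reached has unknown status. The absence of a day-14 limit in 8.2 and its presence in 8.3 should be reconciled so that sites know what to do with a later death. This concerns a secondary endpoint and does not touch the Ang-2 analysis.

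**What to change.** - **Section 9.1, label.** State that the deficit-frequency and z-score comparisons are among tested survivors, and show them beside mortality by arm.
- **Section 9.1, added analysis.** Pre-specify death or deficit by 6 months in all randomised children, with both components reported. A child known to be alive but untested stays missing and is counted as such.
- **Section 9.1, z-scores.** Add a rank-based sensitivity analysis with deaths ranked worst. Do it within age group or test, because 9.1 says that the two age groups take different tests and levels of impairment cannot be compared directly between them.
- **Section 4.9, 6-month CRF.** Add vital status: alive, dead with date, or unknown.
- **Sections 8.2 and 8.3.** Reconcile the SAE form required for every study death with the day-14 limit on post-discharge reports.

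The cost is one CRF field, one added analysis with a ranked sensitivity analysis, and some wording. The drawback is that the composite mixes death with deficit, so it cannot be reported without its components.
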